### Statistical method

A p-value <0.05 is regarded as significant. SPSS statistics will be used for processing.

Non-adherent data are not anticipated for this trial. Prevention of missing values will be handled by telephone checks. If any missing values remain, an analysis will be made of the cause (completely at random/at random/not at random). An intention to treat analysis will be performed.

Comparison between the two interventions can be subdivided in three periods; Pre-operative, per-operative en post-operative comparison.

### Pre-operative

Body Mass Index (BMI), VDS pain score at rest, pain score while exercising and VDS cosmetic score, comorbidity and daily workload. Differences in baseline characteristics will be measured and presented in a baseline characteristics table. The Mann–Whitney test is used for continuous data and the Pearson’s chi-square/Fisher’s exact test for categorical data.

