### Calculation of random sample size

The primary outcome is the number of complications that require treatment. These are defined in detail further in the protocol. The occurrence of complications up to 23% is described [4]. Trials involving patch repair report a much lower complication rate, but the number of trials is significantly less. It is assumed that a conventional procedure leads to a complication in 20% of the cases [4,20]. The hypothesis is that this is reduced to 10% if a patch is used for repair. At a significance level of 5% and a power of 90%, the random sample size is 137 patients per group in a bilateral t-test. In the result analysis a Mann–Whitney parametric test will be used to evaluate a normal distribution. Therefore, the sample size must be increased by 15% [21]. Taking a minimum of 10% loss-to-follow-up into account as well, the total number of patients to be randomized becomes 346.

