#### Questionnaire P1 – by the patient – preoperative

Collected data: height, weight, VDS pain score at rest, pain score while exercising and VDS cosmetic score, comorbidity and daily workload.

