### Post-operative

Occurrence of complications and pain score at rest and pain score while exercising (VDS), the use of analgesics at that time, cosmetic (VDS) and signs of recurrence (1,3,12,24 months post-operative). The Mann–Whitney test is used for continuous data and the Pearson’s chi-square/Fisher’s exact test for categorical data. If possible a Spearman’s correlations are used for analysis of relations between the (sub) groups (comorbidity, chronic post-operative pain patients and recurrence).

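### Baseline significance tests are uninformative, and the unadjusted complication test leaves out centre, BMI and comorbidity: a modest loss of efficiency, not a bias

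*Protocol article*

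**What the plan says.** All places are in the protocol article.

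- **Statistical method** sets p<0.05 as significant and divides the comparison of the two interventions into three periods, of which the pre-operative period is one.
- **Pre-operative** lists BMI, pain at rest, pain on exercise, cosmetic score, comorbidity and workload. It states "Differences in baseline characteristics will be measured and presented in a baseline characteristics table". That sentence alone describes only a table. The sentence after it assigns Mann–Whitney tests to continuous variables and chi-square/Fisher tests to categorical ones.
- **Questionnaire P1** is the source: "Collected data: height, weight, VDS pain score at rest, pain score while exercising and VDS cosmetic score, comorbidity and daily workload". Under Participants it is completed before surgery. Under Randomisation the envelope is opened only in theatre.
- **Post-operative** opens its list with "Occurrence of complications and pain score at rest and pain score while exercising (VDS") and assigns the same family of tests. No regression or stratified analysis is named anywhere. Comorbidity has one other use, in Spearman correlations to be done where feasible.
- **Abstract, Methods/Design** says that randomisation is stratified by centre.

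**The concern.** Two choices are open to question.

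1. Baseline values precede allocation, so any difference between arms arises by chance. A p-value for that difference answers no open question. Whether an imbalance matters depends on its size and on how prognostic the variable is, and a p-value measures neither.
2. Centre is used to allocate patients but not to compare them. BMI and comorbidity are plausible predictors of operation-site complications, are recorded before allocation, and cannot be influenced by the unblinded surgeon. Leaving all three out of the primary comparison gives up some precision in a trial that has little to spare on its own assumptions.

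**Working it through.** **Inputs from the document (Calculation of random sample size).** Control rate: "It is assumed that a conventional procedure leads to a complication in 20% of the cases". Patch rate: "The hypothesis is that this is reduced to 10% if a patch is used for repair". Two-sided 5%, 90% power. Stated size: "the random sample size is 137 patients per group in a bilateral t-test". Then 15% is added for the Mann–Whitney test and 10% for loss, giving 346.

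**Input not in the document.** The prognostic strength of BMI and comorbidity for complications. Assumed R² 0.01 to 0.10.

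**Step 1: the plan's own figure.** The inflation reproduces: 2 × 137 × 1.15 × 1.10 = 346.6. The starting figure does not. With mean rate 0.15, the pooled two-proportion formula gives

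n = [1.96·√(2·0.15·0.85) + 1.2816·√(0.2·0.8 + 0.1·0.9)]² / 0.10² = (0.9897 + 0.6408)² / 0.01 ≈ 266 per arm.

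The unpooled (263), arcsine (261) and continuity-corrected (286) versions do not give 137 either.

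**Step 2: unadjusted power.** Evaluable per arm: 173 × 0.90 = 155.7.

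z = (0.10·√155.7 − 0.9897) / 0.5 = (1.2478 − 0.9897) / 0.5 = 0.516, so power = 69.7%.

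The shortfall from 90% is about 20 points. At 137 per arm power is 64.1%; at 173 with no loss it is 74.3%.

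**Step 3: power with adjustment.** Approximation: effective n = 155.7 / (1 − R²), put into the formula of step 2.

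| R² | Power | Gain over 0.697 |
|---|---|---|
| 0.01 | 0.7015 | 0.4 points |
| 0.02 | 0.7059 | 0.9 points |
| 0.05 | 0.7194 | 2.2 points |
| 0.10 | 0.7425 | 4.5 points |

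R² needed to reach 90% by adjustment alone: 1 − 155.7/266 = 0.41.

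**Step 4: check by simulation.** 3,000 trials per setting, 156 per arm, one normally distributed covariate score, unadjusted z test against the likelihood-ratio test in a logistic model.

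| R² (AUC), control arm | Unadjusted | Adjusted |
|---|---|---|
| 0 (0.50) | 0.694 | 0.701 |
| 0.014 (0.58) | 0.704 | 0.715 |
| 0.038 (0.64) | 0.699 | 0.716 |
| 0.091 (0.71) | 0.693 | 0.737 |
| 0.133 (0.74) | 0.689 | 0.755 |

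The standard error of each entry is about √(0.7·0.3/3000) = 0.008. The first row shows that about 0.7 points come from the change of test alone. The last row lies beyond the assumed range. The simulation agrees with step 3.

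**Step 5: baseline tests.** Six listed variables, with comorbidity counted as one: 1 − 0.95⁶ = 1 − 0.735 = 0.265 if independent. Positive correlation between the pain items would lower this.

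**Step 6: events.** 156 × 0.20 + 156 × 0.10 = 46.8, about 47.

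**The case against.** The strongest reply is that nothing in the primary analysis is invalid. After randomisation, chi-square or Fisher is a sound test. Chance imbalance is already allowed for in its type I error, and covariate adjustment is an option that an article may leave to an analysis plan. The first two points stand in full. The third stands only in part, because the article does not leave the matter open: it names the tests for both the baseline and the post-operative data.

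Other parts of the reply also stand:

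- A reader might infer that the baseline data serve only for balance tests. They do not, since comorbidity also enters the Spearman correlations. Those correlations add nothing to the primary estimate.
- A reader might infer that baseline p-values will be used to judge the randomisation or to pick covariates. No section says so. The text is silent on what follows a significant result.
- The gain rests on an assumed prognostic strength. It was simulated with a single covariate score and a likelihood-ratio test, not with the exact model and risk difference proposed below.
- About 47 events is not many, and the sample-size section itself says that patch trials report much lower complication rates. Centre terms use up part of that information, and the number of centres is not given.

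**Conclusion.** The point holds as a low-cost improvement, not as a fault of validity. The baseline tests are uninformative and can go. The unadjusted primary test is valid but less efficient than it could be: about 70% power, against roughly 70% to 74% with adjustment, which is a gain of about 0.5 to 5 points. This assumes 20% v 10%, 10% loss and R² of 0.01 to 0.10.

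Two stronger readings are not supported. One is that the missing adjustment biases the result; randomisation protects against that. The other is that adjustment would rescue the power. The 20-point shortfall comes from the figure of 137 per group and belongs to the sample-size section. Without adjustment, 90% power needs 266 evaluable per arm, or 532 / 0.90 = 591.1, rounded up to 592 randomised.

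Of the three omitted factors, centre has the firmest grounds in the document, because it is the stated stratification factor. BMI and comorbidity rest on plausibility.

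**What to change.** **Pre-operative.** Present baseline data descriptively by arm and delete the tests.

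**Post-operative.** Pre-specify the primary comparison as a logistic model for any complication, with device, centre (small centres pooled by a rule set in advance), BMI (linear) and any comorbidity (yes/no). Report a standardised risk difference with 95% CI. Keep the unadjusted chi-square as a supporting analysis. State that covariates are not chosen from baseline p-values.

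**Calculation of random sample size.** Correct this separately; the change above does not replace it.

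**Cost.** Analysis wording only; no new data are needed. A few missing heights, weights or comorbidity entries will need simple imputation. With k centre groups the model has 3 + (k − 1) = k + 2 coefficients besides the intercept, set against about 47 events or fewer. That limits how many centre groups can be kept.

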### Per-operative

Presence of incarceration, resection of the hernia protrusion, number of fingers for the width of the herniation orifice, the need of widening the herniation orifice, closure of fascia over mesh, presence of adhesions when placing the device intraperitoneally, operation duration, VDS ease, possible reasons protocol violation. The Mann–Whitney test is used for continuous data and the Pearson’s chi-square/Fisher’s exact test for categorical data.

### Post-operative

Occurrence of complications and pain score at rest and pain score while exercising (VDS), the use of analgesics at that time, cosmetic (VDS) and signs of recurrence (1,3,12,24 months post-operative). The Mann–Whitney test is used for continuous data and the Pearson’s chi-square/Fisher’s exact test for categorical data. If possible a Spearman’s correlations are used for analysis of relations between the (sub) groups (comorbidity, chronic post-operative pain patients and recurrence).

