**Methods/Design:**

346 patients suffering from an umbilical or epigastric hernia will be included in a multi-centre patient-blinded trial, comparing mesh repair with patch repair. Randomisation will take place for the two operation techniques. The two devices investigated are a flat pre-peritoneal mesh and a Proceed Ventral Patch®. Stratification will occur per centre. Post-operative evaluation will take place after 1, 3, 12 and 24 months. The number of complications requiring treatment is the primary endpoint. Secondary endpoints are Verbal Descriptor Scale (VDS) pain score and VDS cosmetic score, operation duration, recurrence and costs. An intention to treat analysis will be performed.

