### Data outcome

A Verbal Descriptor Scale (VDS) is a scale of consecutive descriptions. The following terms are used in the VDS pain score, from which patients can choose to express the level of pain: None, Mild, Moderate, Severe.

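### The VDS pain and cosmetic scores are compared without naming them ordinal and without using the matching pre-operative score or centre, so these secondary comparisons may lose power.

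*Protocol article*

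**What the plan says.** Data outcome defines the pain scale as four words with which patients "express the level of pain: None, Mild, Moderate, Severe". No levels are given for the cosmetic scale.

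Questionnaire P1, completed before surgery, records "height, weight, VDS pain score at rest, pain score while exercising and VDS cosmetic score, comorbidity and daily workload". The same pain and cosmetic scores are collected again on D2, P2, D3 and P3.

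The Pre-operative section gives the P1 scores one use: "Differences in baseline characteristics will be measured and presented in a baseline characteristics table".

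The Post-operative section lists complications, VDS pain at rest and on exercise, analgesic use, VDS cosmetic score and signs of recurrence at 1, 3, 12 and 24 months. It then assigns tests in one sentence: "The Mann–Whitney test is used for continuous data and the Pearson’s chi-square/Fisher’s exact test for categorical data". No covariate, model or stratified test is named there.

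The abstract ranks the outcomes: "Secondary endpoints are Verbal Descriptor Scale (VDS) pain score and VDS cosmetic score, operation duration, recurrence and costs". It also says that randomisation is stratified by centre. The Design section names postoperative pain in the trial's aim.

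**The concern.** An ordered four-level score is neither continuous nor simply categorical, and the sentence that assigns the tests offers only those two classes. The class decides whether the order of the levels counts. Mann–Whitney uses the order. A chi-square test on a 2 × 4 table (3 degrees of freedom) does not: it gives the same result if the four words are shuffled. Leaving the class open also leaves a choice of test that could be made after the data are seen.

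Separately, each patient's pre-operative score on the same scale is in hand but has no role in the between-arm comparison, and neither has centre. Where the earlier score predicts the later one, setting it aside leaves explainable variation in the comparison.

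At stake is the ability to detect a difference in pain, which the trial's aim names but for which no effect size or power is stated, and to a lesser extent in cosmesis.

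**Working it through.** **Plan's own figure.** There is none for the VDS. The only sample size in the article is for complications (20% against 10%), so nothing can be reproduced for pain or cosmesis.

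**Inputs from the article.** 346 randomised, 10% loss to follow-up, two arms, two-sided 5% level. Evaluable per arm: 346 × 0.9 / 2 = 155.7, taken as 156.

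**Assumed inputs (not in the article).**
- A normal latent score, cut into four levels.
- Control-arm levels of 55/30/12/3% (A) or 80/14/5/1% (B).
- Pre-operative levels of 25/40/25/10%.
- A latent shift towards less pain in one arm of 0.35 or 0.45 SD. For A this moves the share with no pain from 55% to Φ(0.126 + 0.35) = 68% or Φ(0.126 + 0.45) = 72%. For B it moves from 80% to Φ(0.842 + 0.35) = 88% or Φ(0.842 + 0.45) = 90%.
- A latent baseline-to-follow-up correlation ρ of 0, 0.3, 0.5 or 0.7.

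**Tests compared.** Pearson chi-square, Mann–Whitney, and a van Elteren test stratified on the pre-operative level. The last sums, over baseline levels k, w_k × [R_k − a_k(N_k + 1)/2] with w_k = 1/(N_k + 1). Here R_k is the rank sum of one arm, a_k its size and N_k the stratum size.

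**Power (%), 2,000 simulated trials per row.** Monte Carlo standard error is at most √(0.25/2000) = 1.1 points.

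| Levels, shift | ρ | Chi-square | Mann–Whitney | van Elteren | MW − chi-square | van Elteren − MW |
|---|---|---|---|---|---|---|
| A, 0.35 | 0 | 55.5 | 72.5 | 71.7 | 17.0 | −0.8 |
| A, 0.35 | 0.3 | 55.3 | 70.5 | 73.8 | 15.2 | 3.3 |
| A, 0.35 | 0.5 | 55.3 | 71.4 | 79.7 | 16.1 | 8.3 |
| A, 0.35 | 0.7 | 57.0 | 73.0 | 87.8 | 16.0 | 14.8 |
| A, 0.45 | 0 | 77.3 | 89.8 | 89.4 | 12.5 | −0.4 |
| A, 0.45 | 0.3 | 80.9 | 91.1 | 92.1 | 10.2 | 1.0 |
| A, 0.45 | 0.5 | 80.2 | 90.2 | 94.8 | 10.0 | 4.6 |
| A, 0.45 | 0.7 | 79.1 | 90.6 | 97.9 | 11.5 | 7.3 |
| B, 0.35 | 0 | 37.4 | 54.7 | 54.1 | 17.3 | −0.6 |
| B, 0.35 | 0.3 | 36.2 | 53.3 | 54.3 | 17.1 | 1.0 |
| B, 0.35 | 0.5 | 34.5 | 52.3 | 57.6 | 17.8 | 5.3 |
| B, 0.35 | 0.7 | 34.9 | 52.7 | 67.2 | 17.8 | 14.5 |
| B, 0.45 | 0 | 55.0 | 72.7 | 72.3 | 17.7 | −0.4 |
| B, 0.45 | 0.3 | 54.1 | 73.1 | 74.0 | 19.0 | 0.9 |
| B, 0.45 | 0.5 | 55.7 | 75.3 | 80.4 | 19.6 | 5.1 |
| B, 0.45 | 0.7 | 56.6 | 74.3 | 84.9 | 17.7 | 10.6 |

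With no shift, rejection rates were about 3 to 6.5% across the tests, so the gains over Mann–Whitney do not come from an inflated type I error. Analysis of covariance on ranks behaved much like van Elteren.

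**Reading the table.**
- Ignoring the order costs 10.0 to 19.6 points in every row.
- Ignoring baseline, given Mann–Whitney, costs nothing at ρ = 0, about 0–3 points at 0.3, 5–8 at 0.5 and 7–15 at 0.7.

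**Limits.** Centre effects were not simulated, and van Elteren stands in here for baseline-adjusted ordinal methods in general. The four-level set-up follows the pain scale; nothing was simulated for a cosmetic scale whose levels are unknown.

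**The case against.** The strongest reply is that the VDS was never meant for chi-square. The other outcomes in the Post-operative list are naturally yes/no, so without the VDS the Mann–Whitney clause would have almost nothing to act on. The article calls the VDS a score, and its sample-size section says that a Mann–Whitney test will be used in the result analysis. On that reading the order is kept.

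This is plausible and largely stands. A reader might infer that the plan sends the VDS to an unordered test and so forfeits 10 to 20 points; the article does not say that, and the loss is conditional. The reply does not close the question, however. The same test sentence appears word for word in the Pre-operative and Per-operative sections, so it reads as a general formula rather than one fitted to this list. The sample-size remark concerns the complication endpoint.

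The second reply is that adjusting for baseline is a preference. An unadjusted rank test is valid in a randomised trial, and omitting a covariate is neither an error nor a contradiction. That stands: the point is about efficiency, not bias.

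Third, covariates and estimates are often left to a fuller document. For estimates this stands: it would be wrong to infer from the named tests that only p-values will be reported, because the article is silent on that. For the tests it does not, since the article itself fixes which are used.

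**Conclusion.** The point holds as one of clarity and efficiency on secondary endpoints. The class of the VDS is left open, and the named tests use neither the matching P1 score nor centre.

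If Mann–Whitney is used, as is plausible, the cost of ignoring baseline runs from nil to about 15 power points depending on a correlation that the article does not give. The larger order-related loss arises only if the VDS is handled as unordered categories. All figures rest on the assumed distributions, shifts and 156 evaluable patients per arm.

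Two broader readings are not supported. One is that power is lost on cosmesis as surely as on pain. Four levels are documented only for pain, and the pre-operative cosmetic score rates a hernia while the later one rates a repaired site, so their correlation, and hence the gain, may be near nil. The other is that the planned comparison is invalid. Randomisation protects it, and the primary endpoint is not touched.

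**What to change.** State in the Post-operative section that the VDS scores are ordinal, and give the levels of the cosmetic scale. Name one order-preserving analysis for each VDS outcome that uses the matching P1 score and centre. This can be a proportional-odds model with treatment, baseline score and centre, reporting the common odds ratio with its 95% CI, or a van Elteren test stratified on baseline level, with the handling of centre stated. Name unadjusted Mann–Whitney, not chi-square, as the sensitivity test.

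The cost is analysis wording only: P1 is already collected, and ordinal regression is available in SPSS, the package the article names. The downsides are small. The proportional-odds assumption has to be checked, and sparse levels or small centres may need pooling under a rule set before the data are seen.

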### Monitoring

A number of medical doctors and researchers contributing in the trial will be inventoried in the starting phase of this trial. Participating centres will be visited for explanation trial. Local monitoring is in the hands of the local investigator. The total overview of informed consent forms will be up-to-date at the coordinating research hospital. Monitoring visits will be made by the surgeon-investigator depending on the pace of inclusion.

### Unexpected turns

Serious side effects and incidents, so-called SUSARs and SAEs, should be reported to the central investigator centre, which will make sure these are reported to the ethics committees.

### Interim analysis

No interim analysis is planned.

### Ethical testing

After approval by local institutional review board (Eindhoven), the protocol along with the name of the surgeon from another hospital will be submitted for local recommendations. Any amendments to the protocol will initially be input at IRB Eindhoven by the principal investigator.

### Post-trial care

Care in the protocol exceeds the care customarily spent in time. Since only general accepted techniques are used, the hospital surgeon will be responsible for possible long-term care.

### Co-investigators

Participating co-investigators will be asked to sign an agreement in which the confidentiality of the data as well as their commitment to the trial.

### Publication

The plan is to create three publications. The primary endpoint with short-term results will be processed in one report. This will be one month post-operatively. The the long-term results will be processed in two another report. One report with one-year results and one with two-year result. In the two-year results report, recurrence will be added as secondary outcome measure. Co-investigators with a contribution of at least 10% of the number of patients required will be asked for co-authorship.

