### Objectives/Endpoints

The primary objective of the MORPHEUS trial is to evaluate whether a ventral patch is associated with fewer complications than in conventional mesh placement for epigastric and umbilical repair. A complication is defined as an undesired development that requires treatment. Complications will be recorded up to three months after the initial procedure and pain up to 24 months post-operative. Secondary endpoints are differences in recurrence, cosmetic score, operation duration and costs.

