#### Questionnaire D2 – by the doctor – 1 month postoperative

Data collected are: complications, use of analgesics at that time, VDS pain score at rest, pain score while exercising and VDS cosmetic score.

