#### Questionnaire P2 – by the patient – 3 months postoperative

Collected data: complications, recurrence, use of analgesics at that time, VDS pain score at rest, pain score while exercising and VDS cosmetic score.

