### Definitions

A complication is defined as an undesired development that requires treatment, related to the operation site, occurring within 3 months postoperative. Treatment could also been initiated by the general practitioner, or other than that by the hospital surgeon. Complications are defined as following:

Extending operation time due to bleeding or other injury during the procedure

Prescribed medication treatment such as antibiotics and pain killers other than paracetamol after discharge

Re-operation such as evacuation of a haematoma, drainage of an abscess, exploration related to pain or intra-abdominal problems, or early recurrence

Wound care which requires more than once a day irrigation of the wound

Hospitalisation longer than scheduled or re-admission

The costs will be calculated post-hoc on the basis of the number of visits to the outpatient clinic, operation duration, costs of prosthesis and complication-related costs up to 2 years after the operation.

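### The publication plan times the primary-endpoint report at one month, but the primary endpoint is defined and collected over three months

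*Protocol article*

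**What the plan says.** Calculation of random sample size names the endpoint: "The primary outcome is the number of complications that require treatment". Two sections fix its window at three months. Objectives/Endpoints states: "Complications will be recorded up to three months after the initial procedure and pain up to 24 months post-operative". Definitions states: "A complication is defined as an undesired development that requires treatment, related to the operation site, occurring within 3 months postoperative".

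Data collection follows that window. The doctor's form at one month (D2) includes complications: "Data collected are: complications, use of analgesics at that time, VDS pain score at rest". So does the patient's form at three months (P2): "Collected data: complications, recurrence, use of analgesics at that time". The later forms, D3 at one year and P3 at two years, list recurrence but not complications.

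The Publication section plans three reports. On the first it says: "The primary endpoint with short-term results will be processed in one report. This will be one month post-operatively". The second and third give the one-year and two-year results, with recurrence added in the two-year report.

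**The concern.** A report with a one-month horizon cannot contain an endpoint that runs to three months. No other listed report takes it over, so the complication data on P2 have no stated place in the publication plan.

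Two things are at stake if the plan is carried out as written. First, events that the definition counts would be left out whenever they occur after month 1. Examples are re-operation for early recurrence, exploration for pain, prescribed analgesics other than paracetamol, and re-admission. Second, the source of the outcome data changes. Under Blinding, the follow-up physician knows the treatment, while the patient is not told until the 24-month questionnaire. Dropping P2 removes the only blinded source for the primary endpoint and leaves D1 and D2, both completed by doctors who know the allocation.

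**Working it through.** **Step 1: compare the stated times (no assumption needed).**

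| Place in the protocol article | Time for complications |
|---|---|
| Objectives/Endpoints | up to 3 months |
| Definitions | within 3 months |
| D2 (doctor) | 1 month |
| P2 (patient) | 3 months |
| D3, P3 | complications not listed |
| Publication, report with the primary endpoint | 1 month |
| Publication, other reports | 1 year and 2 years |

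The Publication entry conflicts with both definitions of the window and with P2. Two of the three months fall outside the report. P2 is the only scheduled form that covers complications in those two months. The Post-operative statistics section lists 1, 3, 12 and 24 months and singles none out for the primary endpoint, so it does not settle the matter.

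**Step 2: illustrate the size.** The document does not say when complications occur, so this step rests on assumptions.

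Inputs from Calculation of random sample size: 20% with mesh, 10% with patch, two-sided 5%, 137 per group, inflated by 15% and then for 10% loss, total 346.

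The plan's own figures: the inflation reproduces, 2 × 137 × 1.15 × 1.10 = 346.6. The starting value does not. The usual two-proportion formula for 20% against 10% at two-sided 5% and 90% power gives 266 per group, not 137. That is a separate issue. It matters here only because it makes the starting power lower than the stated 90%.

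Sizes used: 346 / 2 = 173 per arm with no loss, and 346 × 0.90 / 2 = 155.7, about 156 per arm, after 10% loss.

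Assumptions: 20% and 10% are three-month rates, and the same share s of complications falls after month 1 in both arms. The one-month rates are then p1 = 0.20(1 − s) and p2 = 0.10(1 − s).

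Power = Φ{[(p1 − p2)√n − 1.96√(2p̄(1 − p̄))] / √(p1(1 − p1) + p2(1 − p2))}, where p̄ is the mean of p1 and p2.

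Worked case, s = 0, n = 156: (0.10 × 12.49 − 1.96 × 0.505) / 0.5 = (1.249 − 0.990) / 0.5 = 0.519, so power is 69.8%.

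Expected events without loss: 173 × (0.20 + 0.10) = 51.9. Events omitted = 51.9 × s.

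| s | Rates | Difference (points) | Power, 156 per arm | Power, 173 per arm | Events omitted of about 52 |
|---|---|---|---|---|---|
| 0 | 20% / 10% | 10 | 69.8% | 74.3% | 0 |
| 10% | 18% / 9% | 9 | 64.4% | 68.9% | 5 |
| 20% | 16% / 8% | 8 | 58.5% | 63.0% | 10 |
| 30% | 14% / 7% | 7 | 52.3% | 56.5% | 16 |

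The drop from s = 0 is 5.4, 11.3 and 17.5 points at 156 per arm, and 5.4, 11.3 and 17.8 points at 173 per arm.

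**The case against.** The strongest reply is that this is one sentence in a publication plan. The endpoint is defined elsewhere, twice and consistently, at three months, and the statistical sections schedule no one-month primary analysis. The one-month remark may be loose drafting, or may refer only to the short-term results that accompany the primary endpoint. This is fair as far as it goes: the sentence does not clearly redefine the endpoint, and the loss of events follows only if it is carried out literally. It does not remove the mismatch, because no three-month report is listed and this is the only sentence that says when the primary endpoint is reported.

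The authors also argue in the Discussion that observer bias will be very small, because D2 and D3 use simple multiple-choice questions. That may limit the harm of relying on doctors' forms, but it does not bring back the events after month 1.

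The power figures are open to objection as well. The share of late events is assumed. The 20% and 10% are not tied to any window in the document, and loss to follow-up by one month may be smaller than by three. These objections stand, so the figures are an illustration and not an estimate.

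A reader might infer two stronger points that the document does not support:

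- **Two competing primary results.** Only one window is defined, and a one-month count does not meet that definition.
- **Two looks at the primary endpoint, despite "No interim analysis is planned".** The primary endpoint is assigned to a single report and no second test of it is planned, so there is no conflict with that statement.

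Nor would the one-month result rest on D2 alone, since D1 may capture intra-operative events.

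**Conclusion.** The Publication section is wrong as written: it contradicts Objectives/Endpoints, Definitions and the content of P2 on the timing of the primary endpoint. This is an internal inconsistency, not a flaw in the endpoint, the data collection or the randomisation, since three-month complications are collected in any case. An unseen analysis plan would not remove a time point that the protocol itself states.

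If the sentence is followed literally, the primary result omits complications in months 1 to 3 and the blinded patients' report. The number of events lost is unknown. If 10 to 30% of complications fall after month 1 equally in both arms, and 20% and 10% are three-month rates, power falls by about 5 to 18 points. Only that drop belongs to this point; the low starting value of about 70 to 74% comes from the sample-size calculation.

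**What to change.** Amend the Publication section to say that the report of the primary endpoint is prepared after the three-month (P2) data are complete for all patients, that the 0–3-month complication rate is the sole primary result, and that any one-month figures are descriptive. Make the change before any outcome data are analysed.

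The cost is a short amendment and about two months' delay to the first report. No new visits, forms or patients are needed, and the planning rates and the total of 346 are unaffected by this change.
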